**Fig. 3 Fig3:**
[figure not shown]
SPIRIT Schedule of enrolment, interventions, and assessments

### Measurement instruments

Figure 3 presents an overview of the assessments points.

#### Demographic variables

In the baseline questionnaire participants’ age, sex, height, weight, education, profession and living with kids (if indicated with yes, the childcare situation is additionally assessed) are assessed. For age, height, and weight mean values and standard deviations as well as the body mass index (BMI) are calculated and frequencies are presented for the variables sex, education, profession and living with kids.

#### Psychosocial determinants of behavior change and habit formation

The following psychosocial determinants are assessed for physical activity, nutrition, and mindfulness behavior. Participants indicate their responses on a six-point Likert scale ranging from 1 (not at all true), 2 (not true), 3 (rather untrue), 4 (rather true), 5 (true) to 6 (absolutely true), if not otherwise specified. The baseline (t0), and post (t14) assessments focus on motivational (i.e., intention, outcome expectancies, self-efficacy) and volitional constructs (i.e., action planning), as well as on habit strength for physical activity, nutrition and mindfulness behaviors. The weekly assessments (t1, t2, t3, t4, t5, t6, t7, t8, t9, t10, t11, t12, t13) put focus on the habit formation process (i.e., self-monitoring, emotional states, context stability, intention, outcome expectancies) for all behavioral domains. Mean values and standard deviations are calculated to build the scales for the psychosocial determinants.

##### Intention

Intention is assessed with two items in accordance with Schwarzer, Schütz, Ziegelmann, Lippke, Luszczynska and Scholz ([63]; e.g., I intend to engage in at least 30 min physical activity with at least moderate intensity (i.e., mildly sweating) in the next four weeks on a nearly daily basis; I intend to eat at least five portions of fruit and vegetables daily in the next four weeks; I intend to practice mindfulness activities at least three times per week in the next four weeks, α = 0.56—0.79).

##### Positive and negative outcome expectancies

Outcome expectancies are assessed with six items (i.e., three positive and three negative) in accordance with Schwarzer, Schüz, Ziegelmann, Lippke, Luszcynska and Scholz [63]. Following the stem “If I engage in physical activity for at least 30 min with at least moderate intensity (i.e., mildly sweating)/ If I eat at least five portions of fruit and vegetables daily/ If I practice mindfulness activities for at least ten minutes daily… in the next four weeks…” participants indicate in how far they expect “to do something good for their health” (positive outcome expectancy) or “to have an additional obligation” (negative outcome expectancy; α = 0.52—0.72).

##### Self-efficacy

Self-efficacy is assessed with five items in accordance with Schwarzer and Renner [64]. Following the stem “I am sure I can engage in at least 30 min of physical activity with at least moderate intensity on an almost daily basis/I am sure I can eat at least five portions of fruit and vegetables/ I am sure I can practice mindfulness activities for ten minutes at least three times per week … in the next four weeks, even if,…” participants indicate how likely it is to engage in the respective behavior even if they are for example “tired” (α = 0.87—0.88).

##### Action planning

Action planning is assessed with two items in accordance with Schwarzer, Schüz, Ziegelmann, Lippke, Luszcynska and Scholz, [63]. Following the stem “For the next four weeks I have concretely planned, …” participants indicate for example “where”, “when” and “how often” they engage in physical activity, eat fruit and vegetables, and practice mindfulness activities (α = 0.79—0.83).

##### Automaticity

Automaticity is assessed with four items by means of the subscale Self-Report Behavioral Automaticity Index from the Self Report Habit Index (SRHI) [65, 66] at baseline and post assessments, and with two items at interim assessments (due to economic reasons). Following the stem “Physical activity/ Eating five portions fruit and vegetables/ Practicing mindfulness activities three times per week for ten minutes … is something” participants indicate on a five-point Likert scale ranging from 1 (do not agree) to 5 (totally agree) if they engage in the behaviors for example “automatically”. The SRHI has proven to be a reliable and valid instrument to measure habit strength for physical activity (α = 0.96) [66].

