### Evaluation design

A one-arm, multicenter mHealth interventional study will be performed. Participants complete all assessments in the app with the same assessment rhythm irrespective of when participants enroll in the study. Upon registration, participants can complete questions on socio-demographic variables, psycho-social determinants (e.g., intention, self-efficacy), physical activity, nutrition and mindfulness as well as health-related outcomes (e.g., back pain). Data will be collected across a 100-day period at four assessment points: baseline (booking date + 0), interim after 4 weeks (booking date + 28) and 8 weeks (booking date + 56) and post-intervention (booking date + 99). Additionally, 11 weekly assessments will be scheduled (booking date + 7, + 14, + 21, + 35, + 42, + 49, + 63, + 70, + 77, + 84, + 91). Participants will receive reminder emails for the baseline and post assessment four days after the respective assessment date (i.e., baseline reminder booking date + 4 days, post assessment booking date + 104 days). Reminders for the remaining assessments are incorporated into the app (via “open tasks”, see Description of the intervention for further information). Outcome data will be the same for all participants, whether they continue or discontinue/deviate from the intervention protocol. One week after the completion of the intervention, a structured interview is scheduled with volunteers to gain insights in participants’ experiences with the app (e.g., practicability, operability, acceptability). Due to economic reasons, the total set of items varies per assessment point. The Fig. 3 presents an overview of the enrolment schedule, the intervention, worksheets and assessments.

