### Statistical power

The required sample size for the primary outcome (automaticity over time) was estimated based on recently published recommendations [78]. The power estimation revealed that a level-2-sample size with at least *N* = 228 participants (i.e., number of required individuals, accounting for 30% sample attrition) and a level-1-sample size of at least *n* = 13 measurement points (i.e., number of repeated measurements) is required to detect medium-sized population effects of *f* = 0.40 [21, 79] with sufficient power (≥ 0.80).

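### Automaticity is an item mean of four items at baseline and post but of two unnamed items at interim, so any analysis that mixes these waves can show a change in item content as a change in habit.

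*Protocol article*

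**What the plan says.** All places are in the protocol article.

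- **Instrument.** The Automaticity section states: "Automaticity is assessed with four items by means of the subscale Self-Report Behavioral Automaticity Index". This form is used "at baseline and post assessments, and with two items at interim assessments (due to economic reasons"). The two items are not named and are not said to come from the four. Responses run from 1 to 5.
- **Scoring.** The section on psychosocial determinants states: "Mean values and standard deviations are calculated to build the scales for the psychosocial determinants". No rule links the two forms.
- **Role.** Statistical power: "The required sample size for the primary outcome (automaticity over time) was estimated based on recently published recommendations". Objectives also makes habit strength over time the primary endpoint.
- **Waves.** Evaluation design uses the word interim for two waves: "interim after 4 weeks (booking date + 28) and 8 weeks (booking date + 56) and post-intervention (booking date + 99"). It continues: "Additionally, 11 weekly assessments will be scheduled". With the two interims, this gives 13 waves (t1 to t13) between baseline (t0) and post (t14).
- **Content by wave.** The section on psychosocial determinants places habit strength at baseline and post ("as well as on habit strength for physical activity, nutrition and mindfulness behaviors"). Its list for the weekly waves ("self-monitoring, emotional states, context stability, intention, outcome expectancies") does not include automaticity.
- **Analyses.** Statistical analysis plans repeated-measures ANOVA and t-tests between successive measurements for hypothesis 1, regressions of post on baseline for hypotheses 2 to 4, and a two-level mixed model with 13 periods for hypothesis 5.

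**The concern.** A mean of four items and a mean of two items lie on the same 1-to-5 scale, but they agree on average only if the two retained items are endorsed exactly as strongly as the full set. Otherwise the score steps when the form changes, with no change in habit.

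The trial's stated main purpose is to understand how habits form. A step up at weeks 4 and 8 that disappears at post looks like early gain followed by loss. A step down looks like a dip with late recovery. Either could be reported as a finding about habit formation. The shorter form is also noisier, so the residual variance would differ by wave.

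**Working it through.** **The plan's own figure.** N = 228 with 30% attrition leaves 228 × 0.70 = 159.6, about 160 participants. The number before attrition cannot be rederived, because the significance level, the intraclass correlation and the target parameter are not given. The point does not depend on N; 160 is used only in step 5.

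**1. Set-up.** Assume no true change. The expected score then shifts by d at two-item waves and by 0 at four-item waves. If the two items are among the four, d is half the gap between the retained and the dropped pair: gaps of 0.2, 0.5 and 1.0 points give d = 0.10, 0.25 and 0.50. These gaps are assumptions, since the article gives no item means.

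**2. Contrasts over days 0, 28, 56, 99 (4, 2, 2, 4 items).**
- Baseline to week 4: d - 0 = +d.
- Week 4 to week 8: d - d = 0.
- Week 8 to post: 0 - d = -d.
- Baseline to post: 0 - 0 = 0.

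**3. Linear trend and curve shape over the same four waves.**
- Mean day 45.75; deviations -45.75, -17.75, 10.25, 53.25; sum of squares 5348.75.
- Cross-product with the form indicator (0, 1, 1, 0): -17.75 + 10.25 = -7.5.
- Bias over 99 days: 99 × (-7.5 / 5348.75) × d = -0.14d.
- A quadratic in time leaves one residual contrast. Its weights are the third divided differences, in units of 10⁻⁶: -6.442, 17.965, -14.832, 3.309.
- Applied to the indicator: 17.965 - 14.832 = 3.133. The sum of squared weights is 595.2, and the indicator's sum of squares about its mean is 1.
- Unexplained share: 3.133² / 595.2 = 0.016. The quadratic therefore absorbs about 98% of the form effect, and curvature can hardly be told apart from item content.

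**4. Other wave sets, if two items were asked at all of t1 to t13.**

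| Waves in the model | Linear bias over 99 days |
|---|---|
| t1 to t13 | 0 (one form throughout) |
| t0 to t14 | -0.006d (curvature still biased) |
| t0 to t13 | 99 × 45.5 / 11147.5 × d = +0.40d |

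In the last row, 45.5 is the mean day and 11147.5 the sum of squares of days 0, 7, ..., 91. The linear bias is thus small when both four-item ends are in the model and larger when only baseline is.

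**5. What d could do to a baseline-to-interim paired test (illustration).** Assumed: person SD 0.8 (cancels in the difference), occasion SD 0.3, item residual SD 0.5, n = 160.
- Variance of the difference: 2 × 0.09 + 0.25/4 + 0.25/2 = 0.18 + 0.0625 + 0.125 = 0.3675.
- Standard error: √(0.3675 / 160) = 0.048.

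| d | d / SE | Rejection, closed form | Rejection, simulation (4,000 runs) |
|---|---|---|---|
| 0 | 0 | 5% | 5.5% |
| 0.10 | 2.1 | 55% | 55.6% |
| 0.15 | 3.1 | 88% | 87.1% |
| 0.20 | 4.2 | 99% | 98.5% |

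**6. Reliability (Spearman-Brown).** Two-item alpha = 0.5α / (1 - 0.5α), with α the four-item value. Assumed α of 0.80, 0.90 and 0.96 give 0.67, 0.82 and 0.92. The article's 0.96 is quoted for the SRHI, and it gives no value for the two-item form.

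**The case against.** The strongest reply is that the article nowhere says the two forms will meet in one analysis. Hypothesis 1 is framed as baseline-to-post change and hypothesis 2 regresses post on baseline; both compare four items with four. The 13 periods of the hypothesis 5 model match t1 to t13, which contain no four-item wave. No hypothesis concerns a plateau or a U-shape. The rejection rates only show that an inserted offset is detected, and nothing in the article indicates how large d is, or that it differs from zero. Shortening a form to spare participants is an openly stated trade-off, and detailed scoring often belongs in an analysis plan.

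Much of this stands. Hypotheses 1a and 2 are free of the artefact, and so is a model whose outcomes are all from t1 to t13. A reader might infer that the whole primary outcome is confounded, or that the hypothesis 5 associations are biased. The document supports neither inference.

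Three things remain.
- Read literally, automaticity is collected at only four waves, with 4, 2, 2 and 4 items, so any trajectory with more than two points that includes baseline or post mixes forms.
- With two waves, a repeated-measures ANOVA and a paired t-test are the same test. Naming both is easier to understand if more waves enter, although the article does not say so.
- Hypothesis 5 concerns next-week habit strength. If the 13 periods supply the predictors, the last outcome is the four-item post score; if they supply the outcomes, none is. The article does not say which.

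Nor is this only detail left for later: the article itself fixes both the changing form and the item-mean score.

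**Conclusion.** The concern holds conditionally. In any analysis that combines four-item and two-item waves, a difference d between the forms appears as +d from baseline to week 4, -d from week 8 to post, and distorted curvature. The affected analyses are the successive-wave t-tests if interims are included, a trajectory over days 0, 28, 56 and 99, and a mixed model that includes t0 or t14.

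A reader might also infer that the overall trend in habit strength is badly biased. Over the four waves it is not: the linear trend moves by about -0.14d and the baseline-to-post change not at all.

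The direction and location of the artefact follow from the design. Its size does not, because d is unknown and the 55% to 98% range rests on the assumed offsets and variances in step 5. This is a cheap improvement to the scoring text. It does not change the sample size and does not undermine the baseline/post analyses.

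**What to change.** 1. Name the two interim items and confirm that they are among the four asked at baseline and post. The article does not say so, and the remedy depends on it.
2. State which waves carry automaticity and which form the primary trajectory. In doing so, reconcile the weekly content list with the 13 measurement points in the power and analysis sections.
3. In any model or test that mixes waves, score habit strength from those same two items at every wave. The artefact is then zero by construction.
4. Keep the four-item score for analyses of baseline and post alone (hypotheses 1a and 2), and as a sensitivity analysis elsewhere.

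The cost is a few sentences of scoring text, with no new data and no change to N. The price is somewhat lower reliability of the two-item score at baseline and post (for example 0.82 instead of an assumed 0.90).

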### Weekly assessments with regard to favorite exercises and tasks

#### Self-monitoring

Self-monitoring of self-chosen favorite exercises is assessed with one single-item for physical activity, nutrition, mindfulness and app-user behaviors. Following the stem “In the last 7 days, on how many days did you practice your favorite exercises?”, participants indicate the frequency of behavioral engagement according to the following scale: 0 (not at all), 1 (once), 2 (twice), 3 (three times), 4 (four times), 5 (five times), 6 (six times) and 7 (daily).

#### Emotional state while executing favorites

Emotional state is assessed with one single item (e.g., “How do you feel while practicing your favorite exercises) for physical activity, nutrition and mindfulness behaviors with response options in the form of smileys ranging from 1 (not at all good) to 5 (very good).

#### Context stability of favorites execution

Context stability is assessed in relation to the favorite exercises for physical activity, nutrition, and mindfulness behaviors with two items each (e.g., “I practice my favorite exercise always in the same context”) with response options ranging from 1 (not at all true) to 5 (absolutely true).

#### Intention

Intentions is assessed with one item (i.e., “I intend to practice my favorite exercise within the next 7 days”). Response options range from 1 (not at all true) to 5 (absolutely true).

#### Outcome expectancy

Outcome expectancy is assessed with one item (i.e., “How satisfied are you with the effects of your physical activity, nutrition, mindfulness favorites on your well-being?”). Response options range from 1 (not at all satisfied) to 5 (very satisfied).

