**Fig. 1 Fig1:**
[figure not shown]
Theoretical framework for the present study based on Schwarzer [25] and Gardner and Lally [26]

Building on this integrated framework, outcome expectancies and self-efficacy beliefs complement the process of intention formation (stage 1). Indeed, before a new behavior becomes automatic, individuals need to set a specific behavioral *goal* (e.g., exercising more, eating healthier). Although the latter initially requires discipline and memory performance it should—over time—become habitual after sufficient repetition of the behavior. Goals have been shown to be important antecedents of action initiation [27]. Individuals most likely form a goal when they anticipate positive consequences as a result of their intended behavior (i.e., outcome expectancies) and feel capable to perform the intended behavior despite barriers (i.e., self-efficacy, [28]). While *outcome expectancies* refer to the perceived physical, affective (self-evaluative) and social consequences of one’s behavior, *self-efficacy* is defined as the ability to control one’s behavior to produce desired outcomes [25]. In terms of intervention strategies, information provision on beneficial consequences of action or letting individuals choose behaviors they feel confident about to execute, set the stage for the formation of habits by establishing a motivational basis [29]. Moreover, research has shown that context-dependent repetition was most likely when individuals formulated goals that were specific, achievable and realistic [30]. In contrast, low quality self-chosen goals that were vaguely defined, specified numerous behaviors, and failed to identify a context for action were suboptimal for habit formation [31, 32].

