### Objectives

The present study outlines the protocol for a longitudinal, multicenter single-arm study among health care professionals investigating the role of theory-based motivational and volitional predictors for healthy habit formation in daily life based on a mHealth intervention targeting physical activity, healthy nutrition and mindfulness behaviors (i.e., engaging in mindfulness techniques and relaxation exercises). The aim of this paper is to outline the study protocol including a detailed description of the mHealth intervention, the evaluation plan, and the study design. The main purpose of this trial is to understand the habit formation process for physical activity, nutrition and mindfulness behaviors and its predictors. As preliminary hypothesis (hypothesis 1 a-e), we expect to find positive changes from baseline to post assessments (i.e., 100 days post baseline) in: a) habit strength, b) motivational constructs (i.e., intention, outcome expectancies, self-efficacy), c) volitional constructs (i.e., action planning), d) health behavior (i.e., physical activity, nutrition, mindfulness behaviors) and e) health status (i.e., stress, back pain, well-being, physical and psychological health, body mass index). For the primary endpoint (habit strength over time) and to understand predictors of habit formation over time, we hypothesize that a) habit strength at post-assessment is predicted by baseline motivational and volitional constructs, controlling for baseline habit strength (hypothesis 2), b) that health behavior and c) health status at post assessment are predicted by motivational and volitional constructs as well as habit strength at baseline (hypotheses 3 and 4, respectively). Finally, we hypothesize that next-week habit strength will show positive associations with behavior-related motivational (5a) and volitional constructs over time (5b).

Additionally, we conduct a process evaluation by evaluating participants’ experiences and satisfaction with the app. For the process evaluation a mixed-methods approach will be applied involving questionnaires and structured interviews. The items addressed in this protocol paper are based on the 2013 Standard Protocol Items: Recommendations for Interventional Trials (SPIRIT) statement [[58]; see Additional file 1].

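### The weekly item named outcome expectancy measures satisfaction with effects already experienced, so hypothesis 5a could credit expectancies with a result that belongs to satisfaction

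*Protocol article*

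**What the plan says.** The theory section of the protocol article (Understanding habit formation and its predictors) places outcome expectancies in the motivational stage, before action. People form a goal "when they anticipate positive consequences as a result of their intended behavior (i.e., outcome expectancies").

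At baseline and post the construct is measured that way (Positive and negative outcome expectancies): "Outcome expectancies are assessed with six items (i.e., three positive and three negative"). The stem is conditional and refers to the next four weeks, and "participants indicate in how far they expect" each consequence.

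Under Weekly assessments with regard to favorite exercises and tasks, the Outcome expectancy paragraph gives one item: "How satisfied are you with the effects of your physical activity, nutrition, mindfulness favorites on your well-being". Answers are given on a five-point scale of satisfaction.

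The Objectives count three "motivational constructs (i.e., intention, outcome expectancies, self-efficacy"). The weekly set is narrower: "i.e., self-monitoring, emotional states, context stability, intention, outcome expectancies) for all behavioral domains". Hypothesis 5a expects the motivational constructs to be positively associated with habit strength one week later. Statistical analysis tests this in two-level linear mixed models, one per behavioural domain.

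**The concern.** One name covers two different measurements. The baseline and post scale asks what a person thinks will happen if they act. The weekly item asks how content they are with what has happened.

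This matters for 5a because self-efficacy is not in the weekly set, which leaves intention and this item as the motivational predictors. Followed as written, a positive coefficient for the item could be reported as outcome expectancies being associated with later habit strength. What it would show is that people who are satisfied with their favourites, or are more satisfied than usual, later report stronger habits. Satisfaction may partly result from practising, and on the protocol's own theory repetition is what builds habit. An association could then arise without any role for expectancy.

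The protocol presents its focus on mechanisms of action as a strength, and Table 1 links outcome expectancies to information about health and emotional consequences. Evidence filed under the wrong construct would appear to support that route.

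**Working it through.** **1. The two measures side by side**

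| | Baseline and post | Weekly |
|---|---|---|
| Items per domain | six: three positive, three negative | one, no negative side |
| Time reference | next four weeks | none stated; effects of favourites so far |
| What is rated | expected consequences | satisfaction with effects |
| Scale | 1 to 6, agreement | 1 to 5, satisfaction |
| Needs experience of the behaviour | no | yes |

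The weekly intention item looks seven days ahead, so the same weekly battery could carry forward wording. The article does not say that satisfaction stands in as a proxy for expectancy.

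**2. Share of the 5a test affected**

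The motivational constructs are intention, outcome expectancies and self-efficacy. Those also listed weekly are intention and outcome expectancies. Over three domains this gives 2 × 3 = 6 weekly motivational predictors, of which 1 × 3 = 3, or half, are the satisfaction item. This is a count of predictors and says nothing about the size of a bias.

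**3. Can the mechanism matter at the planned size?**

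The protocol gives no effect sizes for this, so the following is an illustration on assumed values. It took 160 persons (228 × 0.70 = 159.6 after the stated 30% attrition) and 13 occasions, with 400 runs per scenario. For person-level practice plus a weekly deviation with autocorrelation 0.3:

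- satisfaction(t) = c × practice deviation(t) + √(1 − c²) × noise + a person-level term, with c = 0.3, 0.5 or 0.7;
- habit(t+1) = 0.5 × habit(t) + 0.15 × practice(t) + 0.7 × noise.

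Satisfaction has no effect on habit. Next-week habit was regressed on satisfaction with person and week means removed and cluster-robust standard errors. The unadjusted coefficient should be near 0.15 × c, that is 0.045, 0.075 and 0.105. The simulation gave about 0.045, 0.073 and 0.107.

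Share of runs significant at the two-sided 5% level, with a true effect of zero:

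| Model | c = 0.3 | c = 0.5 | c = 0.7 |
|---|---|---|---|
| Satisfaction alone | about 68–71% | about 99% | 100% |
| Plus prior-week habit | about 74–76% | about 99–100% | 100% |
| Plus practice, measured without error (with or without prior-week habit) | about 4% | about 5–6% | about 5–7% |
| Plus practice, reliability 0.7 (with or without prior-week habit) | about 14–16% | about 27–29% | about 62–69% |

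Adjusting for practice is therefore what controls the confounding, and adjusting for earlier habit does not. The planned practice measure is a single self-report item on days practised in the last seven (Self-monitoring), so the last row may be closer to reality than the third.

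**The case against.** Four stronger readings are tempting, and the documents do not support them.

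- **That 5a will give a false positive.** Hypothesis 5a is lagged and worded as an association, and the limitations section says that effectiveness cannot be evaluated in this uncontrolled design. A satisfaction rating in one week does precede habit strength in the next.
- **That practice is left out of the model.** Statistical analysis names weekly behaviour among the level-1 variables and enters all cognitions and covariates together. Practice days are collected weekly under the self-monitoring label and may well be in the model. The text does not say so explicitly, nor that they are held constant when this coefficient is read.
- **That the item measures the result of the past week's practice.** It has no recall window, unlike the self-monitoring item. It presupposes some experience of the favourites and no more.
- **That weekly and baseline expectancies will be compared.** No such analysis is planned. The prospective scale serves hypotheses 1b and 2 to 4, and the weekly item serves 5a. The shared name invites confusion in the report, but that is a labelling risk.

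The simulated rates may also overstate the problem. Automaticity refers to general targets, whereas satisfaction and practice refer to self-chosen favourites, so the common cause may be weaker than assumed. The Automaticity section describes baseline, post and interim measurement, while Statistical analysis speaks of weekly habit strength, so the 13-point series used above is not secure.

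It can be added that the theory section speaks of perceived consequences and that satisfaction may feed later expectations. That would make satisfaction a related construct. It would not make it the one the protocol's own scale asks about.

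These arguments limit the claim about bias. None of them removes the mismatch between label and item.

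**Conclusion.** The concern holds as a matter of labelling and interpretation. The weekly item measures outcome satisfaction, and it supplies one of the two weekly motivational predictors for 5a in each domain. Its coefficient, however well modelled, cannot support a statement about outcome expectancies as the protocol defines them.

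A spurious positive association through practice is plausible in direction, on the assumption that practice raises both satisfaction and habit. Its size is unknown. Under the assumed effects above it runs from about the nominal 5% error rate, with practice measured perfectly and adjusted for, to near-certain significance with no adjustment. The protocol does not fix where in that range the planned model would fall.

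The point deserves correction before analysis, because it changes what the trial may conclude about expectancies. It does not affect the intention part of 5a or the hypotheses that use the baseline scale.

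**What to change.** 1. Rename the weekly item outcome satisfaction wherever it is listed, and do not count its coefficient as evidence for outcome expectancies under 5a.
2. State that weekly practice days, already collected, enter the 5a model as a level-1 covariate when this coefficient is read. Use the count reported at the same assessment as the rating, since it looks back over the preceding seven days; practice in the following week could lie on the path to habit.
3. Only if weekly data collection has not started, the item may instead be reworded as an expectation for the next seven days, in line with the baseline scale. Rewording later would split the series.

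Renaming and naming the covariate add no burden for participants. The price is that 5a then tests weekly intention as its only motivational construct, and the report should say so. Adjustment for a single self-reported practice item removes confounding only in part, so the satisfaction coefficient should still be described as an association.
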